### 2.9. Sample-Size Estimates

The sample-size calculation is based on the primary endpoint: “the detection probability for each group.” The detection probabilities were estimated as follows: standard treatment at 2.8% and automated continuous ECG monitoring at 15.8%, based on prior studies [20]. To establish the non-inferiority of the single-lead patch monitor with a significance level (alpha) of 5% and a power (1-beta) of 80%; each group requires 55 patients, considering a 20% drop-out rate. The calculation was performed using the Power and Sample Size website (http://powerandsamplesize.com/Calculators/Compare-2-Proportions/2-Sample-Non-Inferiority-or-Superiority, accessed on 22 November 2021). Given that this study adopts an intention-to-treat approach, our intended analysis includes cases of participant drop-out, excluding situations where a subject actively requests data removal. The first enrollment of the AVANT-GARDE commenced in April 2023, and the recruitment ended in 2024 with 116 participants.

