## 1. Introduction

The growing prevalence of atrial fibrillation (AF) coincides with the global increase in the elderly population and ranges from 0.4% to 2% among adults [1]. AF, a common arrhythmia, often becomes apparent only after a severe or fatal cardioembolic event. Conventional Holter monitoring, particularly in cases without a clearly identified high-risk cardioembolic source, demonstrates low AF detection rates. Moreover, in patients with traditional atherogenic stroke, recurrent stroke is often associated with AF-related pathologies [2]. Therefore, the early detection of AF is critical for the effective prevention of recurrent events.

In approximately one-third of ischemic stroke (IS) cases, there is no immediately identifiable embolic cause, leading to classification as an “embolic stroke of undetermined source” (ESUS). Notably, over 30% of ESUS patients are found to have underlying paroxysmal atrial fibrillation (pAF) [3]. However, the rate of AF detection via short-term ECG monitoring in these patients is only about 2–3%, suggesting that AF frequently remains undetected. Long-term monitoring using implantable loop recorders (ILRs) achieves detection rates of approximately 23–30%. Although the 2023 European Stroke Organization (ESO) guidelines recommend more than 48 h of continuous cardiac monitoring with an ILR for AF screening in all patients with IS and ESUS [4], its invasive nature limits widespread use [5]. Consequently, echocardiographic indicators such as left atrial (LA) enlargement and laboratory markers like NT-proBNP are used as supplementary tools for AF detection.

The 2020 guidelines from the European Society of Cardiology recommend the use of wearable devices for single-lead ECG recording, with a Class Ia recommendation for AF diagnosis confirmation [6]. Furthermore, a comprehensive systematic review and meta-analysis, which included 47 studies, supports a non-invasive rhythm monitoring strategy as an initial approach before adopting invasive techniques [7]. Based on these findings, a non-invasive single-lead wearable monitoring device may be more sensitive and effective for AF diagnosis than traditional Holter monitoring, thereby reducing the need for repeated ECG tests.

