### 2.10. Statistical Analysis

For baseline variables, bivariate relationships will be examined by employing McNemar’s test for categorical variables and paired samples *t*-tests or Wilcoxon signed-rank test for continuous variables, presented as either means with standard deviations or medians with interquartile ranges, depending on their distribution. The primary outcome will be analyzed comparatively between the single-lead monitoring group and the control arm using McNemar’s test for paired binary outcomes. Effect sizes will be presented as risk differences with corresponding 95% confidence intervals, derived from the discordant pairs. This approach directly reflects the open-label paired design of the trial.

During the 12-month observation period, Kaplan–Meier curves will be generated for each arm and compared using a log-rank test to evaluate potential differences. The Statistical Package for the Social Sciences (SPSS version 26.0, IBM SPSS Statistics, Armonk, New York, NY, USA) will be employed for statistical analyses. A *p*-value < 0.05 is deemed statistically significant.

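### Section 2.9 sizes the trial for non-inferiority without a stated margin, but section 2.10 plans a paired test of difference, so the quoted 80% power does not describe the planned test

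*Protocol article*

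**What the plan says.** **Sizing (section 2.9).** The sample size is set "To establish the non-inferiority of the single-lead patch monitor with a significance level (alpha) of 5% and a power (1-beta) of 80"%. The assumed detection probabilities are "standard treatment at 2.8"% and "automated continuous ECG monitoring at 15.8"%. The result is 55 patients per group, allowing for 20% drop-out. The web calculator cited is for two independent proportions, non-inferiority or superiority. No margin is given, and the sidedness of the 5% is not stated. The section adds that recruitment ended in 2024 with 116 participants.

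**Analysis (section 2.10).** "The primary outcome will be analyzed comparatively between the single-lead monitoring group and the control arm" by McNemar's test for paired binary data. Risk differences with 95% confidence intervals come from the discordant pairs, and significance means p<0.05. The section calls the design paired, which agrees with section 2.7, where patients are monitored with both devices.

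**Aim (section 1).** The background says that a wearable device "may be more sensitive and effective for AF diagnosis than traditional Holter monitoring". The aim that follows is neutral: to evaluate detection with the patch in comparison with Holter.

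**Primary population (section 3).** The primary outcome is restricted to ESUS. Section 2.4 also admits patients with large-artery or small-vessel stroke who have left atrial enlargement.

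**The concern.** Sections 2.9 and 2.10 address different hypotheses and different designs. McNemar's null hypothesis is that the two devices detect AF equally often in the same patients. Rejecting it shows a difference. Failing to reject it does not show that the patch is non-inferior. A confidence interval for the risk difference could show that, but only against a margin fixed in advance, and the article states none.

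Two things are at stake. First, the 80% power figure was computed for a non-inferiority comparison of two separate groups, so it tells the reader nothing about the paired test of difference that will be run. Second, if that test is not significant, nothing in the article prevents a margin from being chosen once the data are known.

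**Working it through.** **1. Can 55 be reproduced from the stated inputs?**

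Inputs from section 2.9: p1 = 0.028 (Holter), p2 = 0.158 (patch), alpha 5%, power 80%, drop-out 20%. Assumptions: 1:1 groups and the usual unpooled normal formula, where m is the allowed deficit of the patch.

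n = [p1(1−p1) + p2(1−p2)] × [(z_alpha + z_beta) / (p2 − p1 + m)]²

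Variance sum: 0.028 × 0.972 + 0.158 × 0.842 = 0.02722 + 0.13304 = 0.16025. Difference: 0.158 − 0.028 = 0.13.

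With m = 0:
- One-sided 5%: 0.16025 × (1.645 + 0.842)² / 0.13² = 58.6, so 59 per group; 59/0.8 gives 74.
- Two-sided 5%: 0.16025 × (1.960 + 0.842)² / 0.13² = 74.4, so 75 per group; 75/0.8 gives 94.

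The pooled formula for a difference gives 61 (77 with drop-out) one-sided and 78 (98) two-sided. None of these is 55.

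**2. Which unstated margins would give about 55?**

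| Drop-out rule | n before drop-out | m at one-sided 5% | m at z = 1.96 |
|---|---|---|---|
| n / 0.8 | 44 | about 2.0 points | about 3.9 points |
| n × 1.2 | 46 | about 1.7 points | about 3.5 points |

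A round margin of 2 points at one-sided 5% gives n = 44.03, which reaches 55 only if rounded down (45/0.8 gives 57). A round margin of 4 points at z = 1.96 gives 43.5, so 44, and 44/0.8 = 55. Several combinations of margin, sidedness and drop-out rule fit, so the margin cannot be recovered.

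**3. What is the power of the planned test?**

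Let a be the proportion of patients with AF found by Holter only. The proportion found by the patch only is then a + 0.13. The article does not give a, so it is varied from 0% (every Holter detection is also a patch detection) to 2.8% (no overlap). If the devices detected AF independently, a = 0.028 × 0.842 = 2.4%. Power is the sum, over the number of discordant pairs d, of Pr(d) times the probability that a two-sided exact McNemar test rejects in favour of the patch.

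| ESUS pairs | a = 2.8% | a = 2.4% | a = 0% |
|---|---|---|---|
| 44 (55 less 20%) | 39% | 41% | 52% |
| 55 | 52% | 55% | 74% |
| 88 (110 less 20%) | about 80% | 82% | 98% |
| 116 (all recruits) | 91% | 93% | 99.8% |

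The case a = 0 can be checked by hand. Five discordant pairs, all favouring the patch, give p = 2 × 0.5⁵ = 0.0625; six give 2 × 0.5⁶ = 0.031. Power is then the chance of at least 6 events in n trials at 0.13, which is 52% for n = 44.

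For 80% power the exact test needs 60 to 89 pairs, or 75 to 112 after dividing by 0.8.

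The article does not say which version of McNemar's test will be used. The uncorrected chi-square version rejects more readily (four discordant pairs to none give chi-square 4, p = 0.046). Its power is 53–84% at 44 pairs and about 64–94% at 55.

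**The case against.** The strongest reply is that superiority implies non-inferiority. If McNemar's test is significant in favour of the patch, with the interval above zero, the patch is non-inferior for any margin. At the planning rates that is the direction to expect. This stands, and it limits the harm to the case of a non-significant result. It does not supply a rule for that case, and it does not make 80% the power of McNemar's test.

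A second reply is that the article condenses a fuller protocol, which may hold the margin. That is possible, and a missing margin alone would be a weaker point. The mismatch does not depend on it: one section sizes for non-inferiority in two independent groups, and the next names a paired test of difference as the primary analysis.

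A reader might infer three stronger things that the article does not support:

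- **That the trial is underpowered.** Each patient supplies both readings, and 116 were recruited. Power for the exact test would be at least 91% if all were evaluable ESUS pairs, and could be as low as 39% with 44. The ESUS count is not given, so neither end is established. Power figures for a two-independent-groups test of difference do not settle this either, since that is not the planned test.
- **That the hidden margin is known and indefensible.** Against a 2.8% Holter rate, a 2-point margin would tolerate a patch rate of 0.8% and a 4-point margin a patch that detects nothing. The article states neither margin, and others fit as well.
- **That superiority is the declared hypothesis.** The remark on sensitivity in section 1 is background and is worded as a possibility. The aim itself takes no side.

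**Conclusion.** The point holds as a conflict between the sizing and the primary analysis. The stated 80% power belongs to a non-inferiority comparison of independent groups with an undisclosed margin, not to the paired test of difference in section 2.10. With no margin supplied, the stated inputs give 59 or 75 per group before drop-out (74 or 94 after), not 55.

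The power of the planned test cannot be stated from the article. It runs from 39% to 99.8% for the exact version over 44 to 116 pairs. That range rests on the article's own detection rates and on an assumed Holter-only proportion of 0% to 2.8%. The analysis can still validly support superiority, and with it non-inferiority, if McNemar's test favours the patch. What is missing is one declared hypothesis, a power figure that matches it, and, if non-inferiority is kept, a decision rule.

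**What to change.** By a dated amendment before the analysis, state one hypothesis in sections 2.9 and 2.10. Either:

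(a) **Superiority.** Declare a two-sided 5% McNemar test in ESUS patients, reported with the paired risk difference and its 95% confidence interval. Remove the reference to non-inferiority. Restate power for the paired test, using the actual number of evaluable ESUS patients and a stated range for discordance, and say which version of the test is meant.

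(b) **Non-inferiority.** Disclose the margin actually entered in the calculator and the sidedness of alpha. Justify that margin against the 2.8% Holter rate. Base the decision on the lower limit of the confidence interval for the paired risk difference, not on the McNemar p-value.

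Neither option needs new patients or data. The cost is that the published power figure will change, and that the amendment must be disclosed as made after recruitment ended. Under (a) this is a change to the stated primary hypothesis, not only to its wording.

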### 2.4. Study Population

Nine hospitals in South Korea participated in this trial: Eunpyeong St. Mary’s Hospital, the Catholic University of Korea, Kangdong Sacred Heart Hospital, Gachon University Gil Medical Center, Hanyang University Myongji Hospital, SMG–SNU Boramae Medical Center, Soon Chun Hyang University Hospital Bucheon, Inje University Sanggye Paik Hospital, and Chosun University Hospital. Each institution is equipped with a dedicated stroke unit and the necessary monitoring and imaging facilities to provide standardized stroke care by experienced specialists.

The absence of diagnosed AF at admission, confirmed through baseline surface ECG, is the key criterion. Eligible participants are as follows: (1) age over 18 years, (2) non-lacunar infarction or non-atherosclerotic cerebral infarction without corresponding artery stenosis > 50% (less than 6 months after stroke onset), (3) no history of AF and showing no AF during initial monitoring, (4) at least 18 h of recording on 24 h Holter monitoring, (5) at least 72 h of recording on a single-lead wearable patch, and (6) who underwent MRI and TTE examination. Subjects were excluded if they (1) exhibited AF on baseline ECG, (2) had valvular heart diseases (e.g., rheumatic mitral stenosis, a mechanical or bioprosthetic heart valve, or mitral valve repair, infective endocarditis), (3) had underlying disease related to AF (recent cardiothoracic and noncardiac surgery (<2 weeks), recent ST-elevation myocardial infarction (MI) (<3 months), pericarditis, myocarditis, hyperthyroidism, electrocution, pneumonia, and pulmonary embolism), (4) had implanted pacemakers, (5) suffered from advanced systemic disease or coexisting neurological/psychiatric conditions, (6) had contact dermatitis or other skin disorders, (7) lacked data on transesophageal echocardiography, or (8) were unable to participate in the study due to other causes.

According to the TOAST classification system, large artery atherosclerosis is defined as corresponding artery stenosis > 50% and small-vessel disease as a subcortical lesion < 15 mm. Patients whose index stroke was LAA or SAO were included if they exhibited LA enlargement.

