## 3. Study Outcomes

The primary outcome was the detection of AF using a single-lead wearable patch compared to a 24 h Holter monitor during the 6-month follow-up period (baseline visit: V0; 6-month visit: V1) in patients with ESUS. The secondary outcome was the comparison of AF detection rates between the two monitoring devices in stroke patients with large artery atherosclerosis (LAA) or small-vessel occlusion (SVO). The tertiary outcome was the occurrence of recurrent stroke among patients with ESUS, given that AF is infrequently diagnosed in individuals who experience multiple recurrent ESUS events (Figure 1).

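### The 80% power in section 2.9 belongs to an independent-groups non-inferiority calculation, not to the paired McNemar test in ESUS patients, and neither 55 nor 116 is identified as an ESUS number

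*Protocol article*

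**What the plan says.** Section 2.9 opens with "The sample-size calculation is based on the primary endpoint". It takes "standard treatment at 2.8% and automated continuous ECG monitoring at 15.8%, based on prior studies", sets alpha at 5% and power at 80%, names non-inferiority of the patch as the aim, and concludes that "each group requires 55 patients, considering a 20% drop-out rate". The calculator it cites is, by its web address, the one for two independent proportions. No non-inferiority margin is given, and it is not said whether alpha is one- or two-sided. The section ends by reporting that "the recruitment ended in 2024 with 116 participants".

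The analysis is described elsewhere:

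- Section 3 defines the primary outcome as patch against Holter over two visits ("baseline visit: V0; 6-month visit: V1) in patients with ESUS"). The secondary outcome is the "comparison of AF detection rates between the two monitoring devices in stroke patients with large artery atherosclerosis (LAA) or small-vessel occlusion (SVO").
- Section 2.4 admits the second cohort to the same trial: "Patients whose index stroke was LAA or SAO were included if they exhibited LA enlargement".
- Section 2.7 has each ESUS patient wear both devices at enrolment and again at 6 months.
- Section 2.10 analyses the primary outcome "using McNemar’s test for paired binary outcomes", with risk differences derived from the discordant pairs and significance at p < 0.05.

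**The concern.** The groups in section 2.9 are the two monitors. Every patient wears both, so no patient belongs to only one group, and two groups of 55 do not exist. The sample size that governs the primary test is the number of ESUS patients with a result from each device, and the text never gives it.

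Three features of the calculation differ from the analysis:

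- **Design:** independent samples against pairs.
- **Hypothesis:** non-inferiority with an unstated margin against a test of difference.
- **Population:** section 2.9 does not name a stroke subtype, whereas the primary outcome is confined to ESUS.

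McNemar power depends on the discordant pairs, about which section 2.9 assumes nothing. At these detection rates few are expected: at 55 pairs, between 55 × 0.13 = 7.2 and 55 × 0.177 = 9.7.

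What is at stake is how the result is read. If the primary comparison is not significant, readers will judge it against a stated 80% that was computed for another test, and against a recruited total that may include patients outside the primary analysis.

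**Working it through.** **Inputs from the article.** Detection 2.8% (standard) and 15.8% (continuous monitoring); alpha 5%; power 80%; drop-out 20% (section 2.9). Paired McNemar test, p < 0.05 (section 2.10), taken here as two-sided.

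**Inputs not given, so assumed over a range.** The non-inferiority margin; the sidedness of alpha in section 2.9; the proportion of patients in whom both devices find AF; the version of the McNemar test; the number of ESUS patients.

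**Step 1. Can 55 be reproduced?** The independent-groups non-inferiority formula is

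n = [p1(1−p1) + p2(1−p2)] × (z for alpha + z for power)² / (p2 − p1 + margin)²

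The variance term is 0.028 × 0.972 + 0.158 × 0.842 = 0.1603.

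- Margin 0, one-sided 5%: 0.1603 × 6.183 / 0.13² = 58.6, so 59 per group, and 59/0.8 gives 74 with drop-out.
- Margin 0, one-sided 2.5%: 75 per group, 94 with drop-out.
- Margin 2 points, one-sided 5%: 44.03, and 44.03/0.8 = 55.04. Rounding up before inflating gives 45, then 57.
- Margin 4 points, one-sided 2.5%: 43.5, so 44, and 44/0.8 = 55.

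The 55 is recovered only with a margin that the article does not state. Every one of these figures is for separate groups.

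**Step 2. Power of the planned test.** Let b be the proportion positive on the patch only, c the proportion positive on the Holter only, and x the proportion positive on both. Then b = 0.158 − x and c = 0.028 − x.

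- Nested (every Holter detection also on the patch): x = 2.8%, b = 13%, c = 0.
- Intermediate: x = 1.4%, b = 14.4%, c = 1.4%.
- Independent: x = 0.158 × 0.028 = 0.44%, b = 15.4%, c = 2.4%.

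With N pairs, the discordant count is K ~ Bin(N, b + c), and the patch-only count given K is Bin(K, b/(b + c)). Power is the summed probability of the outcomes that reject at two-sided 0.05 in favour of the patch.

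| ESUS pairs | Exact: nested / intermediate / independent | Uncorrected: nested / intermediate / independent |
|---|---|---|
| 44 | 52% / 45% / 41% | 84% / 65% / 56% |
| 55 | 74% / 61% / 55% | 94% / 75% / 67% |
| 80 | 96% / 84% / 77% | 99.5% / 90% / 84% |
| 116 | 99.8% / 96% / 93% | 100% / 98% / 95% |
| Pairs for 80% | 60 / 74 / 85 | 42 / 62 / 74 |

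The row for 44 is 55 × 0.8, which applies only if drop-out removes the whole pair. The row for 116 applies only if every recruited patient is an analysable ESUS patient.

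The two tests differ because so few discordant pairs are expected. In the nested case the uncorrected test rejects on 4 pairs all favouring the patch (4/√4 = 2 > 1.96), where the exact p is 2 × 0.5⁴ = 0.125. The exact test needs 6 (2 × 0.5⁶ = 0.031).

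**Step 3. What this means for the 116.** For the exact test, 60 to 85 analysable pairs are 60/116 = 52% to 85/116 = 73% of those recruited. If drop-out did remove pairs, the enrolled ESUS numbers would be 60/0.8 = 75 to 85/0.8 = 106.25, rounded up to 107, or 65% to 92%.

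**The case against.** Several points on the other side stand.

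- **ESUS may be intended.** Section 2.9 says that its calculation rests on the primary endpoint, which section 3 defines in ESUS. The 55 can then be read as a loosely worded ESUS target. That supplies a population but not the power: at 55 ESUS pairs the exact test reaches at most 74%, and the uncorrected test exceeds 80% only when concordance is high.
- **Drop-out need not cost pairs.** Minimum recording times on both devices are entry criteria (section 2.4), and section 2.9 keeps drop-outs in the analysis. A patient lost before 6 months still has a baseline pair. The 44-pair row is therefore conditional, and 55 is the fairer reading.
- **Independence is an extreme.** The devices are worn concurrently at baseline (section 2.7), so most AF on the Holter should also appear on the patch. The truth probably lies nearer the nested end. The article does not say where.
- **The split of the 116 may be reported.** Figure 1 is not shown here and its legend names ESUS, LAA and SVO, so it may carry the counts. The text does not.

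A reader might infer more than the article supports. It does not present 116 as having met a target of 110, and it does not credit LAA or SVO patients to the primary power; it attaches the 80% to 55 per group. Nor do the entry rules exclude a very high ESUS share: section 2.4 permits LAA and SVO patients with left atrial enlargement but sets no minimum number of them.

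**Conclusion.** The point holds as a mismatch between the sample-size statement and the primary analysis. The 80% comes from an independent-groups non-inferiority calculation with an unstated margin, the primary test is a paired test of difference in ESUS patients, and neither 55 nor 116 is identified as an ESUS number.

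At 55 ESUS pairs the exact test falls short of 80% at every concordance considered. The uncorrected test passes or fails depending on concordance. These figures rest on the article's two detection rates, a two-sided 5% level and the assumed concordance range.

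A reader might go on to conclude that the trial is underpowered. That is not shown. The number of ESUS patients among the 116 is not in the text, and with 85 or more analysable pairs either version of the test would reach 80% even under independence. The stated power is unsupported, not shown to be too low.

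**What to change.** In section 2.9:

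1. Replace the requirement of 55 per group with the number of ESUS pairs needed for the planned paired McNemar test, stating the assumed discordant rates (for example 13%/0% to 15.4%/2.4%) and whether the test is exact or uncorrected.
2. State how many of the 116 are ESUS patients and restate the power at that number over the same range. Say whether the 20% drop-out removes pairs or only the 6-month recording.
3. State that LAA and SVO patients do not count toward the primary sample size.
4. Align the hypothesis across sections 2.9 and 2.10: either the objective is a difference tested by McNemar, and the non-inferiority wording goes, or it is non-inferiority, and a margin and a matching paired analysis are given.

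The cost is a rewording, a count from the enrolment log and a short recalculation. The restated power may turn out below 80%. No further enrolment is proposed, and the secondary LAA/SVO comparison can keep its test; nothing in this point requires it to become descriptive.
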